### Patient randomization

To preserve allocation concealment, randomization will be performed using a random treatment generator hosted on a dedicated, publicly available trial website (http://www.peritonealvac.com/). When an eligible patient is identified by the attending surgeon, this website will be accessed by a member of the operating room team and the patient’s last name and hospital number will be entered. The random treatment allocation will then be announced such that the attending surgeon can perform the indicated method of TAC. Variable block size randomization will be performed to ensure equal numbers of patients in each treatment group. Day 1 is considered the day of randomization.

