## Methods/Design

### Overview

The Intra-peritoneal Vacuum Trial is a single-center RCT, which will intraoperatively allocate critically ill or injured adults to TAC with either the ABThera™ or Barker’s vacuum pack after damage control laparotomy for intra-abdominal sepsis or injury. Although the trial in itself may not be sufficient to establish superiority of the ABThera™ over the Barker’s vacuum pack, we hypothesize superiority, and will examine for evidence of this in hypothesis tests. The CONSORT flow diagram
[57] and an overview of the study design are presented in Figures 
1 and
2, respectively.

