### Sample size

No clinical data yet exist on the effect of negative pressure peritoneal therapy on the inflammatory response after damage control laparotomy for intra-abdominal sepsis or injury. Thus, estimates are not available to allow accurate sample size estimation. We therefore propose to undertake a study among a convenience sample of 46 adults. As there are approximately 40 to 50 patients who undergo damage control laparotomy and open abdominal management per year at our institution, this trial should be able to be completed within a 2-year time period.

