### Statistical analyses

All continuous variables will be summarized using histograms and measures of central tendency to determine their underlying distribution before statistical descriptions or analyses are conducted. Means (with standard deviations) and medians (with interquartile ranges) will be used to summarize normal and skewed data, respectively. Non-correlated means and medians will be compared using t-tests and Wilcoxon rank sum tests while dependent means and medians will be compared using paired t-tests and Wilcoxon signed rank tests. Differences in proportions will be compared using Fisher’s exact test and risk ratios with associated 95% confidence intervals.

For the analysis of the primary endpoint, we will use a mixed-effects repeated measures linear model to compare the effects of the ABThera™ and Barker’s vacuum pack on changes in plasma IL-6 concentration at 24 and 48 h after TAC dressing application
[75,76]. For longitudinal studies, mixed-effects models have previously been shown to be superior to conventional last-observation-carried-forward approaches for handling missed observations during follow-up
[77,78]. This approach will also be used to compare the plasma concentrations of TNF-α and IL-1, -8, -10, and −12 between groups at 24 and 48 h in the analysis of secondary endpoints.

Multidimensional analysis will be used to assess whether the allocated TAC dressing has an effect on the collective peritoneal and plasma mediator profiles of the study patients. Principal components analysis will be used to reduce the mediator concentration variables into a smaller set of components that account for most of the variability in the data. Component scores will subsequently be calculated along the reduced number dimensions, after which we will attempt to distinguish between patients treated with the ABThera™ and Barker’s vacuum pack using discriminant or latent class analysis. A similar approach will be performed in order to relate inflammatory mediator concentrations to outcomes.

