Results will be stratified according to the primary indication for damage control laparotomy (intra-abdominal sepsis or abdominal trauma). While clinical efficacy and safety data will be analyzed according to intention-to-treat methods, mediator data will be examined using per-protocol techniques, with per-protocol treatment being defined as the allocated TAC dressing having been in place for at least 24 h. As the number of conducted statistical tests will be large, we will use the false discovery rate (FDR) procedure developed by Benjamini and Hochberg to restrict the proportion of incorrectly rejected null hypotheses to 0.05
[79-81]. All tests will be two-sided, and only those with an FDR-corrected *P* value (that is q-value) <0.05 will be considered statistically significant
[79]. Stata version 12.0 (Stata Corp., College Station, TX, USA) will be used for all analyses.

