This trial has limitations. Although we will be combining the inflammatory mediator concentrations and outcome data for patients with both intra-abdominal sepsis and injury, which may be different, we will stratify our analyses to examine if differences exist between patient diagnoses. Moreover, as the primary objective of this trial is to explore the influence of active abdominal therapy on the systemic inflammatory response among critically ill or injured adults, we will principally use a per-protocol method of analysis. As this method of analysis may not be appropriate or as clinically useful for the exploration of safety and efficacy, we will also utilize an intention-to-treat method of analysis when comparing these endpoints. Importantly, however, as we were unable to estimate the required sample size, we may be underpowered to detect differences in the plasma pro-inflammatory mediator concentrations (or clinical and safety endpoints) among patients randomized to TAC with the ABThera™ *versus* Barker’s vacuum pack.

In conclusion, the Intra-peritoneal Vacuum Trial will be a single-center RCT. Results from this study will lead to an improved understanding of the effect of active negative pressure peritoneal therapy on the systemic inflammatory response to intra-abdominal sepsis or injury after damage control laparotomy. The study will also gather pilot information needed to inform creation of a future multicenter RCT comparing clinical outcomes among those undergoing TAC with the ABThera™ *versus* the Barker’s vacuum pack after damage control laparotomy.

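### The pooled IL-6 model is described without a term for sepsis versus trauma, although the trial combines these groups, says they may differ, and balances the arms only on total numbers

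*Protocol article*

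**What the plan says.** The Overview describes a mixed population, allocated to "TAC with either the ABThera™ or Barker’s vacuum pack after damage control laparotomy for intra-abdominal sepsis or injury". The Inclusion criteria do not restrict or cap either indication.

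Patient randomization gives the balancing method: "Variable block size randomization will be performed to ensure equal numbers of patients in each treatment group". No stratification factor is named. The only patient details said to be entered on the website are surname and hospital number.

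For the primary endpoint, Statistical analyses states that "we will use a mixed-effects repeated measures linear model to compare the effects of the ABThera™ and Barker’s vacuum pack" on changes in plasma IL-6 at 24 and 48 h. The same approach is used for the secondary cytokines. Neither sentence mentions indication.

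Indication appears later in that section: "Results will be stratified according to the primary indication for damage control laparotomy (intra-abdominal sepsis or abdominal trauma"). The limitations paragraph of the Discussion gives the reason. It says the trial will combine data from "patients with both intra-abdominal sepsis and injury, which may be different, we will stratify our analyses to examine if differences exist between patient diagnoses".

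Clinical data lists the indication for damage control laparotomy among the items recorded. Sample size states: "We therefore propose to undertake a study among a convenience sample of 46 adults".

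**The concern.** Indication is the one factor by which the authors choose to stratify their results, yet it appears in neither the allocation nor the description of the pooled primary model. With 46 patients, the arms can by chance receive noticeably different mixes of sepsis and trauma. If IL-6 follows a different course in the two conditions, part of the pooled difference between dressings would then reflect case mix.

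The between-indication variation, which the trial records, would also stay in the error term. That matters in a small sample with no power calculation, which the Discussion says may be underpowered.

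Separate sepsis and trauma results do not repair the pooled figure. Each is a smaller comparison answering a different question, namely whether the findings differ by diagnosis.

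**Working it through.** **Inputs from the protocol.** Total 46, a convenience sample. Sample size says "estimates are not available to allow accurate sample size estimation", so there is no planned effect, SD or power to reproduce. Equal arms are intended, hence 23 and 23.

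**Assumptions, because the protocol gives no figure.** The number of septic patients S among the 46, and the difference D between sepsis and trauma in IL-6 change, in within-indication SDs. Indications are taken to arrive in no order related to the allocation sequence. The calculation uses one time point.

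**Step 1: chance of imbalance.** The number of septic patients in one arm, k, is hypergeometric (46 patients, S septic, 23 drawn). The gap in sepsis share is |2k − S|/23.

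- S = 23: the possible gaps are 1/23, 3/23, 5/23, 7/23 and so on. A gap of at least 20 points means 14 v 9 or worse (5/23 = 22 points), with probability 0.238. A gap of at least 30 points means 15 v 8 or worse (7/23), with probability 0.076.
- S = 16 or 30: the probability of at least 20 points is 0.120. The attainable gaps jump from 4/23 (17 points) to 6/23 (26 points), so this is in effect the chance of 26 points or more.

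Mediator data are analysed per protocol (allocated dressing in place for at least 24 h), so even the overall balance from blocking is not guaranteed for IL-6. For illustration, if 18 per arm remained and half were septic, the chance of at least 20 points would be about 0.32.

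**Step 2: shift in the unadjusted difference.** Shift = D × gap. The standard error within indication is √(2/23) = 0.295 SD. At a gap of 5/23:

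| D (SD) | Shift (SD) | Shift / SE | Conditional type I error |
|---|---|---|---|
| 0.25 | 0.05 | 0.18 | about 5.2% |
| 0.5 | 0.11 | 0.37 | about 5.8% |
| 1.0 | 0.22 | 0.74 | about 7.5% |

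The last column is Φ(s − 1.96r) + Φ(−s − 1.96r), where s is shift/SE and r = √(1 + 0.25D²) allows for the between-indication variance left in the estimated SD. For D = 1: r = 1.118 and 1.96r = 2.19, so Φ(0.74 − 2.19) + Φ(−0.74 − 2.19) is about 0.075. With a 7/23 gap and D = 1 it is about 12%.

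**Step 3: precision.** With an even mix, adjustment multiplies the residual variance by 1/(1 + 0.25D²), which is 0.98, 0.94 and 0.80 for D = 0.25, 0.5 and 1.

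Simulation (10,000 runs per setting, linear model, even mix, true effect 0.85 SD) gave power of about 79% with the term at every D. Without it, power was 80%, 78% and 71% for D = 0.25, 0.5 and 1.

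**Step 4: error over all randomisations.** The same simulations with no true effect gave type I error of 0.049 to 0.053, with or without the term.

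**The case against.** The strongest reply is that the article is condensed. Its sentence on the primary model names a class of model and lists no covariates, so a fuller plan may already include indication. That stands as a caution: the absence of the term is a statement about this text only. The text does say what stratification is for, however, and that purpose is to compare diagnoses. It does not say that the pooled estimate is adjusted.

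Four stronger readings are tempting, and the documents do not support them.

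- *The pooled comparison is biased.* It is not. Valid randomisation keeps the unadjusted test near 5% overall (Step 4). What remains is a shift in the particular trial obtained, and lost precision.
- *Sepsis and trauma differ strongly in IL-6.* The Discussion says only that they may be different, and Table 1 lists IL-6 as raised in both settings. The modelled outcome is change, with blood drawn just before the dressing is applied, so baseline may absorb part of any difference.
- *Uneven arms within a stratum undermine the stratified results.* A 14:9 split does not confound that stratum's comparison by indication. It costs about 5% in variance: (1/14 + 1/9)/(2/11.5) = 1.05.
- *Randomisation should be restratified.* Trial status reports 37 patients enrolled, so at most 46 − 37 = 9 could be affected. The Discussion explains that the interface was kept simple to avoid delay in theatre.

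It is also fair that adjustment gains almost nothing if D is small. At D = 0.25 the simulated power was marginally higher without the term.

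**Conclusion.** The point holds in a limited form. As described, the pooled IL-6 analysis leaves out the factor that defines the mixed population and by which the authors stratify their results. Nothing in the allocation method protects against imbalance in it.

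Under an assumed even mix, roughly one trial in four would show a gap of 14 v 9 or worse. At that gap the unadjusted difference moves by 0.05 to 0.22 SD for an assumed D of 0.25 to 1 SD. The power recovered by adjustment ranges from nothing at 0.25 SD to about 8 percentage points at 1 SD.

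Both the sepsis share and D are assumptions. If the two groups have similar IL-6 change, the issue is negligible. It is worth acting on because the correction is almost free and uses data already collected, not because the planned test is invalid.

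**What to change.** In Statistical analyses, state that the pooled mixed models for IL-6 and for the secondary cytokines include primary indication (sepsis or trauma) as a fixed effect, and that the indication-adjusted estimate is the primary result. Keep the separate sepsis and trauma results, labelled as the examination of heterogeneity between diagnoses. Fix this before the mediator data are analysed by arm.

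The cost is one degree of freedom per model. If D is in fact close to zero, a chance 14 v 9 imbalance makes the adjusted estimate about 5% more variable: 1/(1 − (5/23)²) = 1.05. No new data are needed, and the randomisation procedure stays as it is.

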### Consent procedures

We were granted a waiver of immediate consent for patient enrollment in the trial because: (1) all of the eligible patients will be intubated, critically ill or injured adults under general anesthesia at the time the decision to perform a damage control laparotomy and TAC is made; (2) it will be impractical for the attending surgeon or investigators to contact surrogate decision-makers as the decision to perform open abdominal management is frequently made intraoperatively, and many trauma patients arrive unidentified (as an ‘unknown male/female’); (3) the TAC dressing must be placed emergently after the decision is made to leave the abdomen open
[59]; (4) the ABThera™ and Barker’s vacuum pack technique are commonly utilized for TAC at the FMC and across North America
[10]; and (5) a recent systematic review by our group found insufficient evidence to suggest that the ABThera™ was superior to the vacuum pack for TAC among critically ill or injured adults requiring damage control laparotomy
[10]. Trained surgical investigators will therefore approach recruited patients after their recovery to obtain delayed, written, informed consent to utilize their data for the study. These investigators will provide a written information sheet and explain the study procedures and that continued enrollment in the trial is voluntary. One copy of the consent form will be given to the patient, one will be kept in their chart, and one will be filed as trial documentation.

### Study interventions overview

The first application of the ABThera™ or Barker’s vacuum pack will be performed in the operating room by the attending trauma or general surgeon while the patient is under general anesthesia.

#### ABThera™ application

The ABThera™ (Figure 
3) will be applied according to manufacturer’s recommendations
[53]. The visceral protective layer will first be folded or cut to size to ensure full coverage of all viscera. It will then be gently inserted into the abdominal cavity, beneath the peritoneal lining of the abdominal wall, ensuring to work the dressing down evenly into both pericolic gutters. The more superficial perforated foam layer will then be torn to size and inserted into the open abdominal wound directly over the visceral protective layer. The adjacent skin will subsequently be sponge-dried, after which the open abdomen drape will be placed adhesive-side down onto the foam and intact skin, covering at least an 8- to 10-cm border of periwound tissue. A 2.5-cm hole will then be cut through the drape, after which the interface pad will be applied. The tubing set will subsequently be connected between the interface pad and the canister located in the negative pressure source. Finally, active negative pressure peritoneal therapy will be initiated at 125 mmHg of negative suction.

**Figure 3 F3:**
[figure not shown]
**The ABThera™ Open Abdomen NPT System.** NPT, Negative pressure therapy.

#### Barker’s vacuum pack application

The Barker’s vacuum pack (Figure 
4) will be applied according to our local institutional guideline and previously published descriptions
[54-56]. At the completion of abdominal operation, a polyurethane sheet will be opened and may be perforated several times with a scalpel or surgical scissors. This sheet will then be placed evenly over the viscera, beneath the peritoneal cavity of the abdominal wall, extending deep into the pericolic gutters. Moistened surgical towels will subsequently be placed over the polyurethane sheet. Two closed-suction, 10-French, flat, silicone, Jackson-Pratt drains will then be placed over the moistened surgical towels. Thereafter, their drainage tubing will be tunneled approximately 3 to 5 cm below the skin in order to exit away from the laparotomy wound. The adjacent skin will subsequently be sponge-dried and covered by a large Opsite™ (Smith & Nephew Inc., St. Petersburg, FL, USA) adhesive film dressing. Finally, the drainage tubing from the two Jackson-Pratt drains will be connected to closed drain bulb suction. The Jackson-Pratt drainage tubing will be removed from these drainage bulbs after the patient arrives in the ICU, and connected to 20 mmHg of negative wall suction.

**Figure 4 F4:**
[figure not shown]
The Barker’s vacuum pack.

#### Reoperation and TAC dressing changes

Although the allocated TAC dressings will be left in place for a duration determined by the attending surgeon, local FMC and international guidelines suggest re-operation with attempts at abdominal fascia closure between 24 and 72 h after initial application
[53,59,62]. If abdominal fascial closure is not safe or possible at this time, then a TAC dressing change is recommended
[53,62]. Surgeons will be free to utilize any TAC device that they feel is most appropriate at the time of the first and all subsequent dressing changes.

### Data collection

#### Peritoneal fluid and blood

On study day 1, just before application of the allocated TAC dressing, 4 mL of peritoneal fluid and 16 mL of blood will be collected. Peritoneal fluid will be taken directly from the peritoneal cavity and then transferred into sodium-heparin-containing vacutainer tubes (Benton Dickinson Biosciences, Oakville, ON, Canada). Blood will be collected from the patient’s indwelling intravascular catheter or via venipuncture into sodium-heparin containing and clot-activating (serum collection) vacutainer tubes (Benton Dickson Biosciences, Oakville, ON, Canada). Sixteen mL of blood will also be drawn on study days 2, 3, and 7, as well as on study day 28 or at hospital discharge (whichever comes first). Whenever possible, 4 mL of peritoneal fluid will also be removed at these times from the tubing set or Jackson-Pratt drainage tubing among patients fitted with an ABThera™ or Barker’s vacuum pack, respectively. Immediately after collection, blood and peritoneal fluid samples will be gently inverted several times and then immediately spun at 1,200 g for 15 min at 4°C in a swinging bucket centrifuge to remove cellular debris. The cell-free supernatants will subsequently be collected, aliquoted into labeled cryopreservation tubes, and frozen at −80°C until laboratory analyses can be performed.

#### Clinical data

Clinical data will be prospectively recorded at the time of enrollment and until study day 28, hospital discharge, or death. We will collect data on baseline patient demographics; past history; indication for damage control laparotomy; injury or illness severity scores (Acute Physiology and Chronic Health Evaluation-II [APACHE-II]
[63]; Sequential Organ Failure Assessment [SOFA]
[64], and Injury Severity Score [ISS]
[65,66]); fluid balance; need for renal replacement therapy and the Risk, Injury, Failure, Loss, and End-stage-kidney-disease (ESKD) (RIFLE) criteria for acute renal dysfunction
[67]; and patient physiology (arterial pH, base deficit, and lactate levels; oxygenation indices and partial pressure of arterial oxygen [PaO_2_]/fraction of inspired oxygen [FIO_2_] ratios; and gastric residual volumes). IAP will also be measured via an indwelling bladder catheter as recommended by the World Society of the Abdominal Compartment Syndrome (WSACS)
[68] every 6 h while the abdomen is open and every 12 h once it has been closed.

### Laboratory analyses

We will quantify the peritoneal and plasma concentrations of 65 different mediators relevant to the inflammatory response (Table 
2). This broad-based approach will be taken in order to minimize bias with regards to which mediators are measured and to gain a better understanding of which inflammatory pathways are activated after damage control laparotomy and intra-abdominal sepsis or injury.

**Table 2 T2:** Groups of mediators to be measured using Luminex® bead-based multiplexing technology

**Bio-Plex Pro™ Human Cytokine 21-plex Assay (Bio-Rad Laboratories)**	**Bio-Plex Pro™ Human Cytokine 27-plex Assay (Bio-Rad Laboratories)**	**Bio-Plex Pro™ Human Acute Phase 5- + 4-Plex Panel Complete (Bio-Rad Laboratories)**	**Bio-Plex Pro™ Human Custom 8-Plex (Bio-Rad Laboratories)**
IL-1α	IL-1β	Ferritin	IL-17F
IL-2Rα	IL-1ra	Fibrinogen	IL-21
IL-3	IL-2	Procalcitonin	IL-22
IL-12 (p40)	IL-4	Serum amyloid A	IL-23
IL-16	IL-5	tPA	IL-25
IL-18	IL-6	α_2_-macroglobulin	IL-31
CTACK (CCL27)	IL-7	CRP	IL-33
GRO-α (CXCL1)	IL-8	Haptoglobulin	sCD-40L
HGF	IL-9	Serum amyloid P	
IFN-α2	IL-10		
LIF	IL-12 (p70)		
MCP-3 (CCL7)	IL-13		
M-CSF	IL-15		
MIF	IL-17		
MIG (CXCL9)	Basic FGF		
β-NGF	Eotaxin (CCL11)		
SCF	G-CSF		
SCGF-β	GM-CSF		
SDF-1α	IFN-γ		
TNF-β	IP-10 (CXCL10)		
TRAIL	MCP-1 (CCL2)		
	MIP-1α (CCL3)		
	MIP-1β (CCL4)		
	PDGF-BB		
	RANTES (CCL5)		
	TNF-α		
	VEGF		

Basic FGF, Basic fibroblast growth factor; β-NGF, Beta-nerve growth factor; CCL2, Chemokine (C-C motif) ligand 2; CCL3, Chemokine (C-C motif) ligand 3; CCL4, Chemokine (C-C motif) ligand 4; CCL7, Chemokine (C-C motif) ligand 7; CCL11, Chemokine (C-C motif) ligand 11; CCL27, Chemokine (C-C motif) ligand 27; CRP, C-reactive protein; CTACK, Cutaneous T-cell-attracting chemokine; CXCL1, Chemokine (C-X-C motif) ligand 1; CXCL9, Chemokine (C-X-C motif) ligand 9; CXCL10, Chemokine (C-X-C motif) ligand 10; eotaxin, Eosinophil chemotactic protein; G-CSF, Granulocyte colony-stimulating factor; GM-CSF, Granulocyte macrophage colony-stimulating factor; GRO-α, Growth-related oncogene-alpha; HGF, Hepatocyte growth factor; IFN-α2, Interferon alpha-2; IFN-γ, Interferon-gamma; IL-1α, Interleukin-1-alpha; IL-1β, Interleukin-1-beta; IL-1ra, Interleukin-1 receptor antagonist; IL-2, Interleukin-2; IL-2Rα, Interleukin-2 receptor-alpha; IL-3, Interleulin-3; IL-4, Interleukin-4; IL-5, Interleukin-5; IL-6, Interleukin-6; IL-7, Interleukin-7; IL-8, Interleukin-8; IL-9, Interleukin-9; IL-10, Interleukin-10; IL-12 (p40), Interleukin-12 beta subunit; IL-12 (p70), Interleukin-12 (active heterodimer of IL-12 (p40) and IL-12 (p35)); IL-13, Interleukin-13; IL-15, Interleukin-15; IL-16, Interleukin-16; IL-17, Interleukin-17; IL-17F, Interleukin-17F; IL-18, Interleukin-18; IL-21, Interleukin-21; IL-22, Interleukin-22; IL-23, Interleukin-23; IL-25, Interleukin-25; IL-31, Interleukin-31; IL-33, Interleukin-33; IP-10, Interferon gamma-induced protein 10; LIF, Leukemia inhibitory factor; M-CSF, Macrophage colony-stimulating factor; MCP-1, Monocyte chemoattractant protein-1; MCP-3, Monocyte-specific chemokine 3; MIF, Macrophage migration inhibitory factor; MIG, Monokine induced by gamma interferon; MIP-1α, Macrophage inflammatory protein-1-alpha; MIP-1β, Macrophage inflammatory protein-1-beta; PDGF-BB, Platelet-derived growth factor-B homodimer; RANTES, Regulated and normal T cell expressed and secreted; sCD-40L, Soluble cluster of differentiation 40 ligand; SCF, Stem cell factor; SCGF-β, Stem cell growth factor-beta; SDF-1α, Stromal cell-derived factor-1; TNF-α, Tumor necrosis factor-alpha; TNF-β, Tumor necrosis factor-beta; tPA, Tissue plasminogen activator; TRAIL, Tumor necrosis factor-related apoptosis-inducing ligand; VEGF, Vascular endothelial growth factor.

The levels of the mediators listed in Table 
2 will be determined using Luminex® technology (EMD Millipore) by an investigator blinded to TAC dressing allocation status. All samples will be screened using a unique combination of the following multiplex kits: Bio-Plex Pro™ Human Cytokine 21-plex Assay, Bio-Plex Pro™ Human Cytokine 27-plex Assay, and Bio-Plex Pro™ Human Acute Phase 5 + 4-plex Panel Complete (Bio-Rad Laboratories). In addition, a Bio-Plex Pro™ Human Custom 8-Plex (IL-17F, -21, -22, -23, -25, -31, -33, and sCD-40L) (Bio-Rad Laboratories) will also be used to provide broadened coverage of Th17 cytokines.

Luminex® combines the sensitivity, specificity, and reproducibility of the Enzyme-Linked ImmunoSorbent Assay (ELISA) with the multiplexing capacity of fluorescent bead immunoassays, thus allowing multiple biomarkers to be measured simultaneously. Using this approach, we will be able to measure, in a cost- and time-efficient manner, a host of analytes using <200 μL of sample (as compared to an ELISA-based approach, which would require >5 mL of sample), while minimizing inter-assay variability. This technology, although new, has been thoroughly tested and validated using human samples
[69]. The biomarkers listed in Table 
2 will be grouped into four panels based on typical sample dilution and assay buffer compatibilities. Standard curves will then be generated and the data analyzed using Bio-Plex Manager Software version 6.0 (Bio-Rad Laboratories).

